# STUDY SUMMARY

| **Study Title:** | Acute Kidney Injury In COVID-19 in Derby, United Kingdom |
| --- | --- |
| **Local Study Reference:** | UHDB/2020/050 |
| **Study Design:** | Retrospective cohort study |
| **Study Participants:** | All patients suspected of COVID-19 admitted to UHDB NHS Trust between |
| **Planner Number of Sites:** | 1 |
| **Planned Sample Size:** | 330 AKI patients |
| **Planned Start Date:** | 13th May 2020 |
| **Planned Study End Date:** | 31^st^ May 2021 |
| **Research Question/ Aims:** | Epidemiology of COVID-19 patients who developed AKI in hospitalised patients in Derby, United Kingdom. |

# ROLES & RESPONSIBILITIES

**Sponsor**

The Sponsor, University Hospitals of Derby & Burton NHS Foundation Trust, take on overall responsibility for appropriate arrangements being in place to set up, run and report the research project. A Division of Responsibilities between the CI and Sponsor outlines the duties that have been delegated to the CI for this study.

# LIST OF ABBREVIATIONS

| AE | Adverse Event |
| --- | --- |
| CI | Chief Investigator |
| CRF | Case Report Form |
| DMEC | Data Monitoring and Ethics Committee |
| GCP | Good Clinical Practice |
| GMP | Good Manufacturing Practice |
| ICF | Informed Consent Form |
| ICH | International Conference on Harmonisation of technical requirements for registration of pharmaceuticals for human use. |
| ISF | Investigator Site File |
| ISRCTN | International Standard Randomised Controlled Trials |
| NHS R&D | National Health Service Research & Development |
| PI | Principal Investigator |
| PIC | Participant Identification Centre |
| PIS | Participant Information Sheet |
| QA | Quality Assurance |
| QC | Quality Control |
| RCT | Randomised Control Trial |
| REC | Research Ethics Committee |
| SAE | Serious Adverse Event |
| SDV | Source Data Verification |
| SOP | Standard Operating Procedure |
| TMG | Trial Management Group |
| TSC | Trial Steering Committee |
| TMF | Trial Master File |

# STUDY FLOW CHART

[figure not shown]

**STUDY PROTOCOL**

# BACKGROUND

On 31^st^ December 2019, a cluster of pneumonia cases were detected in Hubei province of China where the cause was unclear. The cause for these cases was subsequently identified as a virus which was referred to as SARS-CoV-2, and the associated disease as COVID-19.^1^ This evolved rapidly into a global pandemic with first case reported in UK as early as on 30^th^ January 2020.^2^ As of 30^th^ April 2020, there have been 3.05 million laboratory confirmed cases world-wide with 161,145 cases in United Kingdom in 539,768 cases tested for COVID-19.^3^ The epidemiology of COVID-19 has differed in China, US and Italy which have different demographic characteristics, testing methods and different ways to curb the spread of infection which can be altered by many things, including behaviour, and the stringent social distancing measure.^4-7^ Though the pandemic started in China, as of 30^th^ April 2020, it has reported only 58.32 cases per million people (pmp) as compared to United kingdom which has reported 2433.8 cases pmp.^3^ This has resulted in different epidemiology of COVID-19 and organ system involvement. Lung involvement in the form of alveolar haemorrhages and respiratory failure has been well document in patients with COVID-19 and has been focus of attention, however, other organs are also affected in COVID-19, but there has been limited information kidney involvement in COVID patients.^5,8^ In initial reports, the acute kidney injury (AKI) incidence in COVID-19 has ranged from 5% to 29% with substantial variation between centres,

possibly due to differences in population demographics and risk factors for AKI.^1,2,5-7^ Initial reports on a small number of patients suggest that SARS-CoV-2 may have a specific effect on the kidneys but it is not yet clear to what extent COVID-19 increases the risk of AKI or how COVID-19 impacts outcomes after AKI.^8,9^

# RATIONALE

The aim of this study is to describe epidemiology of acute kidney injury developing in COVID-19 disease.

Urinary sediment abnormality has been described in COVID-19 patients, but this has also been reported in many critically unwell patients.^9^ In the previous SARS pandemic the reported incidence of AKI was 6.7% with a high mortality of over 90%.^10^ However, SARS-CoV-2 is a is a novel betacoronavirus belonging to the sarbecovirus subgenus of Coronaviridae family and its effects on kidneys are not well known. Careful monitoring of kidney disease and renal replacement therapy (RRT) is extremely important to manage resources which may become scarce during this pandemic.

# OBJECTIVES AND OUTCOME MEASURES/ ENDPOINTS

## Objectives

Primary objective

The primary objective is to describe the epidemiology of acute kidney injury associated with COVID-19 in patients admitted to hospital.

Secondary objectives:

To investigate the association between patient characteristics and patient outcomes in patients admitted with COVID-19.

## Outcome

The primary outcome is acute kidney injury in patients with COVID-19 disease.

Secondary outcomes will include all-cause mortality, need for ventilatory support, admission to ICU, length of stay.

# STUDY DESIGN

This is a retrospective, cohort study of patient data collected during routine care in the hospital settings.

# STUDY SETTING

This is a retrospective, single centre, cohort study of patients with suspected COVID-19 admitted in UHDB Foundation Trust and who had COVID-19 swab sent between 5^th^ March 2020 and 13^th^ May 2020.

# ELIGIBILITY CRITERIA

## Inclusion Criteria

All patients who are admitted to the hospital with suspected COVID-19 infection between 1^st^ March 2020 and 13^th^ May 2020 and who meet following criteria will be included

1. Adult patients greater or equal to 18 years of age.
2. Swab results available for SARS CoV-19
3. Patients admitted to the hospital as per the national screening criteria

## Exclusion Criteria

The following patients will be excluded from the study

1. Paediatric patients as defined by age of <18 years of age
2. Swab results which are awaited
3. Patients on haemodialysis or peritoneal dialysis

# STUDY PROCEDURES

## Recruitment

### Patient Identification

As this is retrospective cohort study, patients will be identified from microbiology dataset which contains details of nasal and pharyngeal swabs sent for real time reverse transcriptase polymerase chain reaction (RT-PCR) for COVID-19.

Eligible patients will be identified from the hospital dataset, if they had COVID swabs sent for RT-PCR. The data in the microbiology dataset will be linked to hospital electronic patient records containing demographic details to obtain identifiable personal information. The dataset will be linked to other data sources like laboratory information management system, electronic patient prescribing and critical care minimum dataset.

### Screening

As this is a retrospective, cohort study, patients will not be screened by the investigators.

In UHDB, patients are suspected of having COVID-19 if the symptoms include fever greater than or equal to 37.8°C and at least one of the following which must be of acute onset: persistent cough (with or without sputum, hoarseness, nasal discharge or congestion, shortness of breath, sore throat, wheezing, sneezing). Patients are admitted to the hospital as per their clinical needs.

AKI will be identified using modified Kidney Disease Improving Global Outcomes (KDIGO) definition of AKI as identified by the NHS England’s algorithm.^11^ The algorithm compares the current measured serum creatinine from an individual patient against the baseline creatinine value defined as either the lowest in the last 7 days or a median of values from the preceding 8 to 365 days depending on availability of previous results stored in laboratory information management system in real time. Urine output will not be used in generating the AKI alerts using NHS England’s AKI algorithm.

## Study Assessments

The data used to perform this study is from usual clinical practice in UHDB NHS Trust and as such all assessments and follow up are as per clinical needs.

## End of Study

The end date for the study will be 31^st^ May 2021

# DATA HANDLING

## System and Compliance

The data will be extracted in excel format and will be stored on encrypted and password protected computer. The data will be checked for errors and duplicates and once accuracy is confirmed, a final version without patient identifiable will be used to analysis on a statistical software.

## Source Data

The data source will be the UHDB NHS Trust’s data warehouse. Data quality reports and checks are completed at various stages in the cleaning and processing cycle, and any duplication is removed.

## Data Workflow

The data will be extracted from data warehouse and will be linked to laboratory information management system, electronic patient records, electronic prescribing cohort and critical care minimum dataset. The data will be hosted on a Trust computer with password protected encryption. The data quality will be checked to ensure validity and the chief investigator will be responsible for the data security.

## Data Access and Security

Data will be stored on an encrypted computer of the chief investigator which is password protected. Direct access will be granted to authorised representatives from the Sponsor, host institution and the regulatory authorities to permit study-related monitoring, audits and inspections. Data will not be transferred outside of the UK.

## Archiving

At the end of the study, following completion of the end of study report, UHDB will securely archive all centrally held study related documentation for a minimum of 5 years. At the end of the defined archive period arrangements for confidential destruction will be made. The data and all essential documents relating to the study will be retained securely for a minimum of 5 years after the end of study, and in accordance with national legislation. All archived documents will continue to be available for inspection by appropriate authorities upon request.

# STATISTICS AND DATA ANALYSIS

Descriptive analysis, percentages and 95% Confidence Intervals will be used initially for estimating the incidence of acute kidney injury in COVID-19 positive patients. Chi-squared or Fisher’s Exact tests will also be performed for categorical variables. Multivariable logistic regression analysis will be used to assess the impact of various baseline variables on acute kidney injury and secondary outcomes including mortality.

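### The primary AKI 'incidence' and its risk-factor model pool AKI present at arrival with AKI arising in hospital; the two should be reported and modelled separately

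*Protocol*

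**What the plan says.** The primary outcome in section 3.2 carries no timing: "The primary outcome is acute kidney injury in patients with COVID-19 disease". Section 9 fixes the measure, its label and its denominator: a percentage with a 95% confidence interval, for "estimating the incidence of acute kidney injury in COVID-19 positive patients".

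Section 7.1.2 fixes the case definition: "AKI will be identified using modified Kidney Disease Improving Global Outcomes (KDIGO) definition of AKI", applied through the NHS England algorithm. The baseline creatinine is "defined as either the lowest in the last 7 days or a median of values from the preceding 8 to 365 days", depending on which earlier results the laboratory system holds.

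The renal exclusion in section 6.2 covers dialysis patients only. Section 6.1 limits entry to patients admitted with suspected COVID-19.

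The purpose is worded in two ways. The Study Summary asks about the "Epidemiology of COVID-19 patients who developed AKI in hospitalised patients in Derby, United Kingdom", and section 2 aims to "describe epidemiology of acute kidney injury developing in COVID-19 disease". The primary objective in section 3.1 is looser: to "describe the epidemiology of acute kidney injury associated with COVID-19 in patients admitted to hospital".

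Section 9 models baseline variables against AKI. Section 9.2.2 names medications and use of critical care among the predictors of in-hospital death, then enters the univariately significant variables in a logistic model with AKI as the outcome.

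**The concern.** A baseline taken before admission allows the first blood sample in hospital to meet the AKI definition. Nothing in the outcome, the case definition or the exclusions sets that event apart from AKI appearing days later. A patient who already has AKI at arrival is not at risk of developing it in hospital, yet stands in both the numerator and the denominator of a figure called an incidence.

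Two things are at stake. The first is interpretation: a reader of the headline figure cannot tell how much of it is prevalence at admission and how much is new risk during the stay. The second is the risk-factor model. Characteristics of patients who arrive with AKI may differ from those of patients who acquire it, and one pooled yes/no outcome averages the two. An in-hospital exposure such as critical care use can also come after AKI. When AKI was present at arrival it must do so, and such a variable then cannot be read as a risk factor.

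**Working it through.** **Setting the sections side by side**

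1. Section 7.1.2: the baseline may be a value from before admission, so the first admission sample can be flagged.
2. Sections 3.2, 6.2 and 9: no onset window, and no exclusion of patients with AKI at arrival. Such a flag therefore enters the numerator.
3. Section 9: the denominator is all COVID-19 positive patients, not those free of AKI at arrival.
4. It follows that the figure is a period proportion of any AKI. This is inferred from the absence of a timing rule; the protocol does not say in words that AKI at arrival is counted.
5. Section 9 speaks of baseline variables for the AKI model. Section 9.2.2 takes variables from univariate screening straight after a list that includes critical care and medications. Nothing limits the AKI model to variables that precede AKI.

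**Illustrating the size**

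The plan gives no figure on this point to reproduce. The planned 330 AKI patients are not used as a numerator, because they are not stated to be COVID-19 positive and section 9.2.4 also includes a COVID-negative AKI control group.

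Inputs:
- *p*, the combined proportion with AKI: 5% and 29%, the ends of the range in section 1, used only as round values.
- *s*, the share of AKI present at arrival: 20%, 40% and 60%. This is an assumption; the protocol gives no value.
- *N* = 1,000 COVID-19 positive patients, also an assumption. It cancels from the risk and matters only for the intervals.

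Formulas:
- AKI at admission among all patients = *s* × *p*
- New-onset risk among those free of AKI at admission = *p*(1 − *s*) / (1 − *s* × *p*)

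| Combined *p* | Share at arrival *s* | AKI at admission | Later AKI / at risk | New-onset risk | Gap (points) |
|---|---|---|---|---|---|
| 29% | 20% | 58/1,000 = 5.8% | 232/942 | 24.6% | 4.4 |
| 29% | 40% | 116/1,000 = 11.6% | 174/884 | 19.7% | 9.3 |
| 29% | 60% | 174/1,000 = 17.4% | 116/826 | 14.0% | 15.0 |
| 5% | 20% | 10/1,000 = 1.0% | 40/990 | 4.0% | 1.0 |
| 5% | 40% | 20/1,000 = 2.0% | 30/980 | 3.1% | 1.9 |
| 5% | 60% | 30/1,000 = 3.0% | 20/970 | 2.1% | 2.9 |

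Wilson 95% intervals for the combined figure at *N* = 1,000 are 26.3% to 31.9% (at 29%) and 3.8% to 6.5% (at 5%). At 29%, all three new-onset risks lie below the interval. At 5%, the risk for *s* = 20% lies inside it and the other two lie below it.

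**The case against.** The strongest reply is that AKI at arrival belongs in the count. Section 3.1 targets AKI associated with COVID-19 in admitted patients, and section 2 ties onset to the disease, not to the hospital door. A patient admitted with acute symptoms whose first creatinine is flagged may well have AKI that developed in COVID-19. This stands: a reader might infer that the plan misclassifies such patients, and the protocol does not support that. It answers neither the label nor the pooled model.

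A reader might also infer that AKI preceding the infection is routinely counted. Section 6.1 admits only patients hospitalised with suspected COVID-19, so someone admitted with AKI for another reason and infected later falls outside the criteria as worded. Section 7.1.1 finds patients by swab without tying swab date to admission date, so such cases are possible, but only as a residual group.

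A third tempting step is to say that the result cannot be compared with the 5% to 29% in section 1. The protocol does not say how those reports treated AKI at admission, so comparability cannot be judged either way.

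Finally, onset windows are often left to a statistical analysis plan, and one may exist. That would excuse missing detail. Here, however, the protocol itself fixes the outcome, case definition, label and denominator, and together they do not give the new-onset quantity that its aim suggests.

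**Conclusion.** The point holds in a limited form. The planned primary figure is the proportion of COVID-19 positive patients with any detected AKI, pooling AKI at arrival with later AKI. Calling it an incidence does not fit an aim phrased as AKI that develops, and the risk-factor model inherits the pooling with no safeguard on the order of exposure and outcome.

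The difference is about 4 to 15 percentage points at a combined 29%, and about 1 to 3 points at 5%, if 20% to 60% of AKI is present at arrival. That share is assumed, so these numbers show how far the two quantities can part, not how far they will. The combined figure remains a legitimate description under the primary objective. What is proposed is a better analysis at low cost, not the correction of an invalid one.

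**What to change.** In sections 7.1.2 and 9:

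- Count only alerts within the index admission, and state how AKI at admission is defined (for example, first alert within a fixed number of hours of arrival).
- Keep the combined figure, but call it the proportion with AKI.
- Report separately (a) AKI at admission among all COVID-19 positive patients and (b) later AKI among those free of AKI at admission.
- Fit the risk-factor model for (b) alongside the overall model, using only variables that precede AKI.
- Tabulate AKI with onset before the first positive swab, but do not exclude it from the main analysis. Swab date is a poor proxy for infection date: a creatinine taken before the swab, or an early false-negative swab, would remove genuine COVID-associated AKI.

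The cost is small. Sections 7.1.1 and 8.3 already link swab, laboratory and patient records, so the work is a comparison of dates, one more table and one more model. The drawback is fewer events in the split model, and so less precise estimates. The split will also be less certain for patients with no stored earlier creatinine, for whom the definition as summarised offers no pre-admission baseline.

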### Outcome Analysis

Univariate analysis will be performed to ascertain any significant association of baseline variables with mortality in patients with COVID-19 disease. Any variables with significant association in univariate analysis will be entered in multivariable logistic regression analysis to ascertain the effects of age, gender, ethnicity, comorbidities, medications, use of critical care and acute kidney injury on the likelihood of in-hospital death. A multivariable logistic regression will be performed to ascertain the effects of variable found to be significant in univariate analysis on AKI as an outcome in COVID-19 disease. All tests will be two-tailed, and p<0.05 will be considered significant. Analysis will be performed on IBM SPSS Statistics for Mac, Version 24.0

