### Analysis Groups

Descriptive analysis will be performed in patients with COVID-19 disease between patients who didn’t have AKI with those who had AKI in COVID-19 disease, between AKI in COVID-19 disease and a control group of patients with AKI with no COVID-19 disease and between survivors and non-survivors in COVID-19 disease. For this, categorical variables will be described as frequency and percentages. Continuous variables will be described as mean with standard deviation or median with inter-quartile range. Means for continuous variable will be compared using t-test if the data is normally distributed otherwise Mann Whitney test will be used. Proportion from categorical variables will be compared with chi square test.

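### Section 9 assigns logistic regression to all secondary outcomes, but length of stay is a duration, and the only other stated test ignores death and the timing of AKI

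*Protocol*

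**What the plan says.** Section 3.2 (Outcome) names four secondary outcomes: "Secondary outcomes will include all-cause mortality, need for ventilatory support, admission to ICU, length of stay". Three are binary and one is a duration. They serve the secondary objective in section 3.1: "To investigate the association between patient characteristics and patient outcomes in patients admitted with COVID-19".

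The opening of section 9 sets the model: "Multivariable logistic regression analysis will be used to assess the impact of various baseline variables on acute kidney injury and secondary outcomes including mortality". It makes no exception for any outcome, and no section gives a threshold that would turn length of stay into a binary variable.

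Section 9.2.2 (Outcome Analysis) then describes two logistic models. One estimates the contribution of several factors, among them "use of critical care and acute kidney injury on the likelihood of in-hospital death". The other concerns the "effects of variable found to be significant in univariate analysis on AKI as an outcome in COVID-19 disease". It names no model for length of stay.

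Section 9.2.4 (Analysis Groups) plans three descriptive two-group comparisons: AKI against no AKI within COVID-19, COVID-19 AKI against AKI without COVID-19, and a comparison "between survivors and non-survivors in COVID-19 disease". For continuous variables it says: "Means for continuous variable will be compared using t-test if the data is normally distributed otherwise Mann Whitney test will be used".

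Section 7.1.2 (Screening) identifies AKI by running each current creatinine against a baseline value in real time. It does not limit AKI to the time of admission.

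**The concern.** A logistic model needs a yes/no outcome. For length of stay the analyst must either choose a cut-off after seeing the data, or abandon the stated model and use the two-group tests of section 9.2.4.

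Those tests bring two further problems when stay is compared by AKI status:

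- **Death ends the stay.** A patient who dies on day 4 and one who goes home on day 4 have the same value. If AKI is associated with death, AKI can appear to shorten stay. The protocol gives reason to expect that association: section 2 cites mortality above 90% with AKI in the earlier SARS outbreak, and section 9.2.2 enters AKI as a predictor of death.
- **AKI takes time to arise.** A patient who stays longer has more days on which AKI can be flagged. Ever-AKI patients will then tend to have longer stays even if AKI has no effect.

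The two mechanisms pull in opposite directions, so neither the sign nor the size of an observed difference could be interpreted. The tests are also unadjusted, whereas section 9 promises multivariable analysis of the secondary outcomes.

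**Working it through.** **1. Outcome type against stated method**

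| Secondary outcome (3.2) | Type | Logistic model applies? |
| --- | --- | --- |
| All-cause mortality | binary | yes |
| Ventilatory support | binary | yes |
| ICU admission | binary | yes |
| Length of stay | duration, no cut-off | no |

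This mismatch needs no arithmetic. The protocol gives no figure for length of stay that could be reproduced.

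**2. Inputs for the illustrations.** From the protocol: 330 planned AKI patients (Study Summary) and a two-sided 0.05 level (section 9.2.2). Everything else is assumed. The comparator of 808 is 330/0.29 − 330, where 29% is the top of the AKI incidence range in section 1. Treating all 330 as COVID-19 patients is also an assumption.

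**3. Death as a competing event, AKI present at admission.** Assume a discharge hazard of 0.09/day in both groups, so that AKI has no effect on discharge, and a death hazard of 0.03/day without AKI. With constant hazards, median stay = ln 2 / (discharge + death hazard).

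- No AKI: 0.693/0.12 = 5.8 days.
- AKI doubles the death hazard: 0.693/0.15 = 4.6 days.
- AKI triples it: 0.693/0.18 = 3.9 days.

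Mann-Whitney with 330 against 808: the standard error under no difference is √[1139/(12 × 330 × 808)] = 0.0189.

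- Doubled: the probability that the AKI stay is the shorter is 0.15/0.27 = 0.556; z = 0.0556/0.0189 = 2.94; rejection rate Φ(2.94 − 1.96) ≈ 84%.
- Tripled: 0.18/0.30 = 0.60; z = 5.3; rejection rate nearly 100%.

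A cause-specific model for discharge alive would have a hazard ratio of 0.09/0.09 = 1 in both cases. The cumulative incidence of discharge alive would show the deaths openly: 0.09/0.12 = 75%, 0.09/0.15 = 60% and 0.09/0.18 = 50%.

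**4. AKI arising during the stay, with no effect on anything.** Assume an exit hazard of 1/40 (death) + 1/12 (discharge) = 0.1083/day and AKI arising at 0.03/day.

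- Never-AKI stay is exponential at 0.1083 + 0.03 = 0.1383/day: median 0.693/0.1383 = 5.0 days.
- Ever-AKI stay is the time to AKI plus the remaining stay: mean 1/0.1383 + 1/0.1083 = 16.5 days, median 13.8 days.

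**5. Different assumptions: a true difference exists.** Lognormal stay (log SD 0.8), survivors' median 10 days with AKI and 8 without, mortality 20% without AKI, 330 against 330 or 800 patients, 300 runs per scenario. Ranges cover the two comparator sizes.

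| Mortality with AKI; median time to death | Approx. median stay, AKI vs none (days) | Mann-Whitney significant, all patients | Significant, survivors only |
| --- | --- | --- | --- |
| 60%; 4 days | 5.7 vs 7.0 | 77–86%, AKI shorter | 68–81% |
| 50%; 6 days | 7.8 vs 7.6 | 6–9% | 77–84% |
| 30%; 8 days | 9.4 vs 8.0 | 67–81%, AKI longer | 84–94% |

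Distortion runs from a reversed sign, through a lost difference, to a modest weakening.

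**6. If stay were dichotomised to rescue the logistic model.** Splitting at 7 days, the AKI odds ratio across all assumed scenarios was 0.71 to 1.39 with deaths at their observed stay, and 1.80 to 3.73 with deaths counted as not discharged alive. The two codings answer different questions, and the protocol does not say which is meant.

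**The case against.** The opening of section 9 is an overview, and section 9.2.2 is the operative text. That section describes logistic models only for death and AKI, both binary, so the broad sentence may simply be loose wording. Section 9.2.4 gives continuous variables a workable test, and its survivor comparison would already describe stay by vital status. No section presents an AKI effect on stay as an inferential aim. Competing-risk modelling of one secondary outcome is often left to an analysis plan, which may exist. For bed use, observed stay regardless of vital status is a legitimate descriptive quantity.

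Much of this stands, and it limits the weight of the point. It does not remove it. The sentence in section 9 names a method for the secondary outcomes, so this is a method fixed badly rather than a detail deferred. The tests of section 9.2.4 are unadjusted, and the survivor comparison is not split by AKI status.

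A reader might infer that resource planning would be misled. The documents do not support that: the Rationale speaks of monitoring kidney disease and renal replacement therapy, and mentions neither stay nor beds.

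**Conclusion.** The point holds for one outcome. Logistic regression does not apply to length of stay as listed, and the fallback two-group test can distort an AKI versus no-AKI contrast of stay in either direction. AKI incidence, mortality, ventilatory support and ICU admission are unaffected, so this should be corrected but is not critical to the study.

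The mismatch between sections 3.2 and 9 rests on the text alone. The size of the distortion rests on assumed death, discharge and AKI rates, and on an assumed comparator size, none of which the protocol gives. With lower mortality and later deaths the direction stayed right and the distortion was smaller. A reader might take the 84% rejection rate or the reversed medians as forecasts for this cohort; they show only what can happen.

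**What to change.** - In section 9, restrict multivariable logistic regression to the binary outcomes: AKI, death, ventilatory support and ICU admission.
- For length of stay, analyse time from admission to discharge alive with in-hospital death as a competing event. Use a cause-specific Cox model with the baseline characteristics as covariates, and report the cumulative incidence of discharge alive beside it.
- Where AKI enters that model, make it time-varying from the first alert, or limit it to AKI present at admission. State which, since the second answers a narrower question.
- In section 9.2.4, tabulate median stay by AKI status separately for survivors and decedents, labelled as descriptive.

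The cost is a change of wording, one additional model and a somewhat harder result to explain. It needs dates of admission, discharge, death and AKI alert. Sections 7.1.1 and 8.3 name the linked sources but do not list these fields, so their availability is likely but should be confirmed. No new patients are needed.
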